##### Clinical progression-free survival (PFS)

Progression is defined as biochemical progression, clinical progression (including loco-regional or distant progression on imaging) or start with hormonal therapy, whichever occurs first.

##### Acute toxicity (up to 3 months) and late toxicity (up to 3 years)

Toxicity will be assessed as reported by the patient (RTOG Acute Radiation Morbidity Criteria using adapted RTOG/EORTC acute Radiation Morbidity questionnaires) and the physician ( Common Terminology Criteria for Adverse Events (CTCAE), version 4.0).

##### Quality of life (QoL)

To evaluate QoL aspects, the European Organization for Research and Treatment of Cancer (EORTC) QoL thirty item score questionnaires (QLQ-C30) will be used, which is a cancer-specific questionnaire focusing on symptoms and side effects of specific diseases and treatments. Furthermore, the EORTC QoL prostate carcinoma module (QLQ-PR25) is used to address the specific impact of treatment-related side effects in prostate cancer.

##### Time to palliative hormonal treatment (ADT)

Time to hormonal treatment is defined as the time from trial randomisation to start of palliative hormonal treatment. Palliative ADT should not be started for biochemical progression without documented clinical progression. In case of symptomatic progression, palliative ADT is mandatory. In case of clinical asymptomatic progression, delayed ADT until progression to a symptomatic state is permitted for men who are well informed (EAU guidelines [1]).

##### Overall survival

Overall survival is defined as the time from the date of randomisation to the date of death from any cause.

*Other secondary endpoints* are disease specific survival, start of second-line treatment, start of second MDRT treatment for new (progressive) oligometastases, and the time to castration-resistance.

### Interventions

#### Radiotherapy treatment (arm 1 and arm 2)

Patients will be treated with stereotactic body radiotherapy (SBRT) to all oligometastases (up to 4). In case of > 2 pelvic lymph node metastases, whole pelvic fractionated radiotherapy (WPRT) treatment is recommended.

Patients with a post-prostatectomy local recurrence on the PSMA PET/CT with up to 4 oligometastases will be treated with SBRT to all oligometastatic lesions or WPRT and with fractionated radiotherapy to the prostate bed.

##### Patient positioning and planning CT acquisition

Patients will be positioned in supine position with indexed head, knee and feet support. Additional immobilization devices, allowing safe treatment delivery, can be used according to the institutional policy. In case of WPRT or prostate bed RT treatment with comfortably full bladder is recommended. An empty rectum is recommended for prostate bed radiotherapy.

A treatment planning CT scan is required to define the clinical target volume (CTV), the planning target volume (PTV) and the critical structures. CT slice thickness should be ≤ 2 mm. For MDRT the treatment planning CT scan should include the entire target volume and the surrounding organs at risk (OAR). For spine cases, with the aim to easily identify vertebrae, the planning CT scan should include sacrum for lower spine or include C1 for upper spine. MRI of the target vertebrae, and at least one to two vertebrae above and below, is suggested for target volume and OAR delineation. In case of WPRT or prostate bed RT, the treatment planning CT scan should include at least the pelvis from the lower part of the second lumbar vertebra (L2) to the lower part of the ischial tuberosities. If MRI is used for co-registration (recommended for prostate bed radiotherapy), the same position for both the planning CT and MRI is recommended.

##### SBRT-MDRT treatment

MDRT will be given with a SBRT technique in 3 fractionation regimens according to the location of the metastases and the surrounding organs at risk: 5 fractions of 7 Gy every other day, 3 fractions of 10 Gy (48 h interval between fractions) or 2 fractions of 12 Gy once a week. An equivalent (hypo) fractionated regimen with a EQD2 ≥ 70 Gy using alpha beta of 3 Gy is allowed.

The prescribed dose preferably covers > 95% of the PTV (V100 > 95%), and should cover at least 90% of the PTV (minor variation, V100 > 90%) (Table 1). In case of violation of dose constraints to the surrounding organs at risk, the prescription will be adapted accordingly.

**Table 1 Tab1:** Three fractionation regimens and the required clinical goals for MDRT using SBRT in the ADOPT trial

Fractions (n)	Total prescribed dose (Gy)	Clinical goal	Minor variation
2	24	•PTV V100% > 95% •PTV V95% ≥ 99%	•PTV V100% > 90% •PTV V92% ≥ 99%
3	30		
5	35		

##### Whole pelvic and prostate bed treatment

The lymph node (LN) PTV will receive fractionated radiotherapy equivalent to 46–50 Gy. An integrated boost to LN > 1 cm will be given up to equivalent dose of 66 Gy if the constraints of surrounding organ at risk are not violated. An equivalent dose of 70–77 Gy should be given to prostate bed PTV synchronically with the oligometastatic lesions. Treatment plans will be regarded as optimal when > 98% of the PTV is covered by the 95% isodose and less than 2% of the PTV is higher than the 107% isodose. Treatment plans are considered as accepted with minor violation if less than 98% but more than 95% of the PTV is covered by the 95% isodose or the 90% to 94.9% isodose covers > 98% of the PTV, and if more than 2% but not more than 5% of the PTV receive a dose higher than the 107% isodose.

##### Target volumes and organs at risk (OAR)

The definition of target volumes will be in accordance with the ICRU (ICRU 62, 83, 91) report [18]. For MDRT the gross tumour volume (GTV) is the visible lesion on planning CT matched with the PSMA PET/CT. There is no GTV-CTV margin for LN advised, and for non-vertebral bone metastases a GTV-CTV margin of 5-10 mm is allowed according to local protocol. For vertebral bone metastases the use of the International Spine Radiosurgery Consortium Consensus Guideline is recommended [19]. The PTV margin advised for MDRT is GTV + 5 mm uniformal margin, but dependent on the local protocol of the treatment centre. The prostate bed and WPRT target volume recommendations are added to Additional File 1. In case of MDRT, OAR are delineated according to the location of metastases (at least up to 2 cm above the PTV). In WPRT and prostate bed RT the OAR concern bladder, rectum, bowel and femoral heads. The organ at risk constraints are added to Additional File 1.

##### Irradiation techniques and position verification

Intensity modulated radiotherapy (IMRT) or use of rotational techniques is mandatory in case of WPRT and SBRT. By definition, only dosimetry obtained by inverse treatment planning is considered as IMRT. IMRT may be performed by using Step-and-Shoot-Technique, Sliding-Window-Technique or Volumetric Modulated Arc Therapy, including MRI-guided radiation therapy systems. Daily image guidance will be used for all treatments.

#### Androgen deprivation therapy (arm 2)

The experimental arm should receive an LHRH-agonist (leuprorelin), for a duration of 6 months. The medication will be given in one administration of 45 mg (subcutaneously), the leuprorelin will be supplied on a physician prescription and administered according to the standard use of this medication for prostate cancer. Flare prevention with an anti-androgen could be used for at least 5 days prior to the first injection of the agonist and should not be continued for longer than 28 days. ADT should start no later than the first day of radiotherapy and no earlier than 12 weeks before the start of radiotherapy. Testosterone levels should be checked at 4 weeks following the first injection. ADT-related toxicity should be managed according to Nguyen et al [20].

No treatments potentially influencing the PSA level should be started before the primary endpoint is reached (metastatic progression). The total duration of ADT is limited to 6 months and is not allowed to be continued afterwards. It is highly recommended not to start ADT in case of biochemical progression without clinical progression.

### Evaluation and follow-up

At baseline the investigations include the collection of patient characteristics, a full medical history including PCa characteristics, and the results of the PSMA PET/CT imaging. Baseline toxicity (physician and patient reported) and QoL (patient reported) are recorded. Baseline laboratory assessments include PSA, Testosterone, Haemoglobin (Hb), and Alkaline phosphatase (ALP). The assessments at follow-up include changes in medical history and medication, WHO-performance score, and regular laboratory assessments. Toxicity and QoL will be regularly monitored, and adverse events are reported. The investigations required at baseline and during follow-up are summarized in Table 2.

**Table 2 Tab2:** Follow up after radiotherapy treatment

Required investigation	Baseline	Treatment period		Follow-up				
			1 m after RT	3 m after RT	6 m after RT	9 m after RT	12 m after RT	Every 6 (up to 36 months) months until progression^b^
Eligibility check	X							
Informed consent	X							
ADT (arm 2)		X						
Patient characteristics/ medical history	X		X	X	X	X	X	X
Laboratory assessment								
PSA	X		X	X	X		X	X
Testosterone	X		X		X		X	X
Hb	X			X	X		X	X
ALP	X			X	X		X	X
Whole body PSMA PET/CT^a^	X						X	Every 12 months
Treatment and dosimetric data		X						
Toxicity & QoL								
CTCAE v4	X	X^c^	X	X	X		X	X
RTOG-EORTC toxicity	X	X^c^	X	X	X		X	X
EORTC-QlQ-25	X				X	X	X	X
EORTC-QLQ-C-30	X				X		X	X
SAE		X	X	X	X	X	X	X^d^

^a^ PSMA before inclusion, at progression and for patients without progression only at 12 and 24 months

^b^ 36 months visit, only lab, EORTC-QLQ-C-30 and CTCAE toxicity criteria

^c^ only in case of WPRT or prostate bed RT, the toxicity measurements should be intended at 4th week of treatment course

^d^ Until 2.5 years after treatment completion

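### After month 12, Table 2 schedules visits only until an unspecified progression, although late toxicity, quality of life, later treatment and survival need data after it

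*Protocol article*

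**What the plan says.** **Schedule.** Evaluation and follow-up, Table 2, lists visits at 1, 3, 6, 9 and 12 months after radiotherapy with no condition attached. One further column follows, "Every 6 (up to 36 months) months until progression". It holds medical history, PSA, testosterone, Hb, ALP, CTCAE and RTOG-EORTC toxicity, both quality-of-life questionnaires, SAEs and the yearly PSMA PET/CT.

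Three footnotes bear on that column:
- Imaging: "PSMA before inclusion, at progression and for patients without progression only at 12 and 24 months".
- Last visit: "36 months visit, only lab, EORTC-QLQ-C-30 and CTCAE toxicity criteria".
- SAEs: "Until 2.5 years after treatment completion".

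No section describes a visit, contact or vital-status check after progression.

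**Endpoints.** The secondary endpoints include late toxicity up to 3 years and quality of life. For palliative ADT, "Palliative ADT should not be started for biochemical progression without documented clinical progression"; the same section lets well-informed men without symptoms delay it until symptoms appear. The Overall survival section says "Overall survival is defined as the time from the date of randomisation to the date of death from any cause", and adds disease-specific survival, "start of second-line treatment, start of second MDRT treatment for new (progressive) oligometastases, and the time to castration-resistance". The section on androgen deprivation therapy asks that no treatment affecting PSA start before metastatic progression.

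**Analysis.** Secondary time-to-event endpoints are compared by Cox regression. The only censoring rule in the article is 30 months, and it applies to the primary endpoint.

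**The concern.** The printed stopping point comes before many of the events that the secondary endpoints are meant to count. Second MDRT is for new or progressive lesions. Second-line treatment and castration resistance follow from treatment that the protocol itself holds back until progression. A delayed start of palliative ADT falls after progression by construction.

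Late toxicity and quality of life are different: they can be measured at any time, but from month 12 the schedule asks for them only in patients who have not progressed.

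If sites follow the table, observation after month 12 ends for a reason tied to prognosis. It also ends at different rates by arm if ADT has the effect the trial is designed to detect. Cox or regression comparisons of the later endpoints would then rest on informative, arm-unequal loss. This matters because the Discussion looks to improved quality of life and possibly lower cancer mortality as consequences of a positive trial.

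**Working it through.** **Inputs** (Sample size section): hazards 0.0330 per month (MDRT) and 0.0205 per month (MDRT + ADT), hazard ratio 0.621, alpha 5%, power 80%, dropout 18% at 30 months, 140 patients per arm.

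**Step 1: reproduce the plan's figures.**
- Hazards: ln(2)/21 = 0.03301 and −ln(0.65)/21 = 0.02051.
- MPFS at 30 months: exp(−30 × 0.03301) = 37.1% and exp(−30 × 0.02051) = 54.0%, as stated.
- Events needed (Schoenfeld, two-sided 5%, 80% power): 4 × (1.960 + 0.842)² / (ln 0.621)², which rounds up to 139.
- Dropout hazard: −ln(0.82)/30 = 0.00661 per month. With dropout as a competing risk, the probability of an observed event by month 30 is h/(h + 0.00661) × [1 − exp(−30(h + 0.00661))] = 57.9% and 42.1%, mean 0.500.
- N = 139/0.500 = 278, against 280 stated.

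The plan's rates are therefore coherent and can be used for the next steps.

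**Step 2: share of patients progressed by month t**, 1 − exp(−ht), no dropout.

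| Month | MDRT | MDRT + ADT | Patients of 280 |
|---|---|---|---|
| 24 | 54.7% | 38.9% | 131 |
| 30 | 62.8% | 45.9% | 152 |
| 36 | 69.5% | 52.2% | 170 |

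At 30 months: 140 × 0.628 + 140 × 0.459 = 88 + 64 = 152. With the planned dropout as a competing risk, 140 patients are observed to progress by month 30 and 155 by month 36.

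**Step 3: follow-up time left uncovered.** Only time after month 12 counts, because the earlier visits have no progression limit. Mean time after progression between months 12 and 36 is 24 − [exp(−12h) − exp(−36h)]/h.
- MDRT: 24 − (0.6730 − 0.3048)/0.0330 = 24 − 11.16 = 12.84 months; 12.84/36 = 35.7%.
- MDRT + ADT: 24 − (0.7819 − 0.4781)/0.0205 = 24 − 14.82 = 9.18 months; 9.18/36 = 25.5%, just below the half before rounding (0.2549), so about 25%.

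**Step 4: if ADT has no effect.** With the control hazard in both arms, 280 × 0.628 = 176 patients would have progressed by month 30, with no imbalance. The arm difference depends on the hypothesised effect; the loss itself does not.

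**Step 5: which progression.** The table does not say. The section on clinical progression-free survival counts biochemical progression as progression, and the Background reports more than 60% biochemical recurrence within 2 years of MDRT. On that reading visits would stop earlier, and for more patients, than in Step 2.

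**The case against.** The strongest reply is that a condensed article often leaves survival and later-therapy follow-up to the full protocol, and that a table of required investigations does not say that participation ends at progression. That stands as a caution: the full protocol may provide for it. But the article does more than stay silent. It prints a stopping condition that clashes with its own endpoints, and the column needs correcting either way.

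The footnotes also give calendar limits, with a 36-month visit and SAE reporting to 2.5 years, and late toxicity is defined to 3 years without mention of progression. These may show that follow-up to fixed dates was intended. Both footnotes belong to the column limited by progression, however, so they create an ambiguity and do not resolve it.

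Three stronger readings are tempting, and the article does not support them:
- **That the endpoints are censored at progression.** No such rule is printed. What can be inferred is that scheduled collection stops.
- **That quality of life and late toxicity would describe only patients who did well.** All visits to month 12 apply to everyone, which covers the 6-month ADT course and the following months.
- **That every late endpoint is affected equally.** Overall survival is a weak example, since death can precede progression and may reach the trial through SAE reports. Palliative ADT or second MDRT begun at the progression assessment can be recorded there. The problem is clearest for delayed ADT, later lines and castration resistance.

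**Conclusion.** The point holds in a limited form. After month 12 the printed schedule stops at an undefined progression, while several declared secondary endpoints need data beyond it. On the plan's own rates about 152 of 280 patients (63% versus 46%) would have progressed by month 30, and about 36% versus 25% of the 36-month window would be uncovered. Late toxicity and quality of life after month 12, and the later-treatment endpoints, would be exposed to informative loss.

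These figures assume that metastases progression ends the visits, that hazards stay constant to month 36, that there is no dropout, and that time since radiotherapy can stand for time since randomisation. The difference between arms also assumes the hypothesised hazard ratio.

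The primary endpoint and N = 280 are not called into question: on this reading the primary event is already recorded when visits stop. The change should be made, but the trial's main comparison does not depend on it.

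**What to change.** Reword the last column of Table 2 to: every 6 months up to 36 months in all patients, irrespective of progression. Apply this to:
- vital status and cause of death;
- start dates of palliative ADT, second MDRT and second-line therapy;
- castration resistance;
- the quality-of-life and CTCAE items already in that column, keeping the reduced month-36 content of the footnote.

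State separately which progression ends the routine PSMA PET/CT. If the full protocol already provides for this, align the table with it.

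The cost is slightly more data collection. Much of it could come from clinical records, a telephone contact or posted questionnaires. No patient's treatment changes and N stays at 280. With 100 of 280 patients randomised by December 2021, a correction made when the article appeared would have served most of the cohort.

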#### Imaging

Follow-up PSMA PET/CT should be performed in case of biochemical progression and for patients without progression at 12 and 24 months after treatment. Biochemical progression is defined as a PSA-value higher than the last value prior to therapy (validated 6 weeks later).

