### Study design

The ADOPT-study is a multicentre open phase III randomised controlled trial. Participating centres are radiotherapy centres in the Netherlands (an updated list is available on ClinicalTrials.gov/ NCT04302454).

All eligible patients will be randomly assigned (1:1) to: MDRT alone (140 patients) versus MDRT + short term ADT (140 patients). (Fig. 1) Patients will be stratified by number of metastases, metastases organ (lymph nodes or bone, in case of both the bone group is applicable) and presence of local recurrence (identified on PSMA PET/CT).

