### Primary endpoint

#### 2.5-year metastases progression-free survival (MPFS)

MPFS is defined as the time from randomisation to the date of metastases progression (appearance of new metastatic recurrence and/or progression of the treated metastases), reported by PSMA PET/CT during the follow-up (date PSMA PET/CT).

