### Statistical analysis

#### Sample size

From a previous meta-analysis, we know that the median progression-free survival in patients treated with MDRT is 21 months [6]. This corresponds to an event rate of 50% in the MDRT group at 21 months. For the MDRT + ADT group we assume a decreased event rate to 35% (65% event-free). Assuming a constant hazard of 0.0330 in the MDRT group and 0.0205 in the MDRT + ADT group, the metastases progression-free survival at 2.5 years is expected to be 37.1% in the MDRT group and 54.0% in the MDRT + ADT group. This is associated with a hazard ratio of 0.621. Assuming an alpha of 5%, power of 80%, and a dropout of 18% at 30 months, we need to recruit 140 patients per treatment arm and 280 patients in total.

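### MPFS is dated by scans that before month 12 depend on a PSA rise, which ADT suppresses in one arm only, so the primary hazard ratio leans modestly towards ADT

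*Protocol article*

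**What the plan says.** All references are to the Protocol article.

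- **Event date.** The primary endpoint section runs MPFS from randomisation to progression "reported by PSMA PET/CT during the follow-up (date PSMA PET/CT".
- **When scans happen.** The Imaging section gives the rule: "Follow-up PSMA PET/CT should be performed in case of biochemical progression and for patients without progression at 12 and 24 months after treatment". Table 2, footnote a, lists the scans as "PSMA before inclusion, at progression and for patients without progression only at 12 and 24 months". The only trigger that the Imaging section defines is a PSA above the last pre-therapy value, confirmed six weeks later. The threshold is the same in both arms.
- **PSA visits.** Table 2 has PSA at 1, 3, 6 and 12 months after radiotherapy (none at 9), then every six months.
- **Treatment difference.** "The experimental arm should receive an LHRH-agonist (leuprorelin), for a duration of 6 months". ADT may start up to 12 weeks before radiotherapy. The same section bars other PSA-altering treatments until metastatic progression, so the authors recognise that a disturbed PSA matters to this endpoint.
- **Analysis.** The primary endpoint analysis is a Cox model on these dates, adjusted for the stratification variables, with censoring at 30 months and a check of proportional hazards.

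**The concern.** The scan rule is worded identically for both arms, but it does not work identically. In arm 1 the early PSA visits act as extra looks for progression. In arm 2 the drug under test holds PSA down during some or all of those visits, so the first effective look may be the 12-month scan.

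A Cox model on scan dates cannot separate later progression from later looking. At stake are the primary hazard ratio and its one-sided error rate in favour of the experimental arm of an open phase III trial. Moving the visit clock would not remove this, because the asymmetry comes from PSA suppression.

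**Working it through.** **1. The plan's own figure.** Inputs: "Assuming a constant hazard of 0.0330 in the MDRT group and 0.0205 in the MDRT + ADT group", and "Assuming an alpha of 5%, power of 80%, and a dropout of 18% at 30 months".
- Hazards: ln 2/21 = 0.0330 and −ln(0.65)/21 = 0.0205, ratio 0.621.
- Events (Schoenfeld, two-sided 5%, 80% power): 4 × (1.960 + 0.842)² / (ln 0.621)² = 31.4/0.227, so 139.
- With exponential dropout of 18% at 30 months, the event probabilities are 0.579 and 0.421, mean 0.500. 139/0.500 = 278, against 280 stated. The sample size reproduces and is not in question.

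**2. One patient.** Assume radiotherapy one month after randomisation in both arms, and a metastasis arising at month 5.
- Arm 1, if PSA has crossed the threshold: the 6-month visit is at month 7, and about 1.5 months for confirmation gives an event at month 8.5.
- Arm 2, with PSA suppressed: the 12-month scan is at month 13.
- Same disease, dated 4.5 months apart.

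**3. Simulation with no true effect.** Hazard 0.0330 in both arms, 18% dropout, censoring at 30 months, unadjusted Cox, equal radiotherapy start. Three inputs are not in the documents and are assumed: q, the share of progressors whose PSA crosses the threshold (0.3 to 0.9); the lag from metastasis to threshold; and how long the trigger stays silent in arm 2.

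| Trigger silent in arm 2 | Null hazard ratio |
|---|---|
| Never (control) | 1.00 |
| At 1 and 3 months only | 0.97 to 1.01 |
| Through 6 months, no lag | 0.98 / 0.95 / 0.92 for q = 0.3 / 0.6 / 0.9 (0.91 at the low end in a second set-up) |
| Through 6 months, mean lag 3 months in both arms | 0.95 to 0.99 |
| Through 18 months, no lag | 0.96 / 0.92 / 0.89 for q = 0.3 / 0.6 / 0.9 (0.87 to 0.98 across set-ups) |

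If every progressor crossed the threshold (q = 1.0, no lag), the ratio would be 0.90 with silence through 6 months and 0.86 through 18 months.

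**4. False wins for ADT.** With about 139 events, SE(log HR) = 2/√139 = 0.170. The chance of a significant result for ADT is Φ(−1.96 − ln HR/0.170):
- HR 0.99: Φ(−1.90) = 2.9%
- HR 0.95: Φ(−1.66) = 4.9%
- HR 0.91: Φ(−1.40) = 8.0%
- HR 0.87: Φ(−1.14) = 12.7%

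Simulated rates agree: about 3% to 8% with silence through 6 months, and up to 12.5% with silence through 18 months and q = 0.9. Runs of 1,500 trials carry a Monte Carlo error of about 0.4 points, and one control run gave 4.0%, so single rates of 3% to 4% should not be read as inflation.

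**5. What the fixed scans recover.** Just before the 12-month scan, apparent MPFS is 94% / 88% / 81% in arm 1 (q = 0.3 / 0.6 / 0.9) against 100% in arm 2. At 30 months both arms show about 44%. The last shared scan is at month 25, and exp(−0.0330 × 25) = 0.438.

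**6. Share of the planned effect.** On the log scale, ln(0.99)/ln(0.621) = 2% and ln(0.91)/ln(0.621) = 20%.

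**7. Later radiotherapy in arm 2.** If ADT lead time puts radiotherapy 2 to 3 months later in arm 2 (assumed; the limit of 12 weeks is 2.8 months), the null ratio is 0.86 to 0.92 and false wins are about 8% to 17%. Part of this is a separate clock effect: with fixed scans only and a 3-month delay, the ratio is already 0.91.

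**The case against.** The strongest case against is about size and certainty.

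- **The 6-month visit is not certainly masked.** Visits count from radiotherapy, and ADT may start up to 2.8 months earlier, so that visit falls 6 to 8.8 months after the injection. The documents give no recovery time. If only the 1- and 3-month visits are masked, the bias all but vanishes. This stands.
- **PSA may lag in arm 1 too.** The lesions behind the baseline PSA are irradiated in both arms. With a mean lag of 3 or 6 months and silence through month 6, q = 0.6 gives 0.96 or 0.98, with false wins of 4.3% or 3.1%. This stands.
- **Fixed scans and the proportional hazards check limit harm.** The scans do. The check may show a gap before month 12 and catch-up at 12, but it would not correct the estimate.
- **This belongs to the SAP.** The remedy could sit there. The trigger, schedule, event date and primary model are all fixed in the article, and together they create the asymmetry.

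A reader might infer that PSA suppression alone could deliver a positive trial, or that the 6-month injection switches off every early look and the 18-month one as well. The documents do not support either. They set scheduled scans in both arms and are silent on the length of suppression, and even the extreme case (0.86) is far from 0.621. That ADT lowers PSA is itself implied by the bar on PSA-altering treatments, not stated.

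**Conclusion.** The concern holds in direction and is modest in size. As the rules are written, arm 1 progression can be dated earlier than the same progression in arm 2, and the Cox hazard ratio is biased towards ADT.

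With equal radiotherapy start and silence through the 6-month visit, the null ratio is about 0.91 to 0.99 and false wins are about 3% to 8% against 2.5%. The ratio is near 1 with silence at months 1 and 3 only, and about 0.87 to 0.98 with silence through 18 months. These ranges rest on assumed values for the threshold share, PSA lag, length of suppression and radiotherapy delay.

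The 30-month proportion hardly moves when radiotherapy starts together. The stated test is the hazard ratio, however, and that does move. The point therefore calls for a binding supporting analysis. It does not invalidate the primary comparison.

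**What to change.** Keep the Cox model as stated, and pre-specify a second MPFS analysis on the looks that both arms share. Require it to agree with the Cox result before benefit is claimed.

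- Use an interval-censored proportional hazards model, or a grouped-time complementary log-log model, with the same stratification covariates. A progression found on a PSA-triggered scan goes to the interval ending at the next scheduled 12- or 24-month scan.
- Define the intervals by actual or planned scan times from randomisation. If arm 2 starts radiotherapy later, a simple grid counted from radiotherapy errs the other way (null ratio about 1.08).
- State how three groups are handled: triggered events after the 24-month scan; patients with a triggered event who drop out before the next scheduled scan (otherwise an event in arm 1 but a censored observation in arm 2); and patients with PSA progression and a negative scan, who should still be counted at the scheduled looks. The Imaging section leaves this last case unclear.

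In simulation with a common radiotherapy start, the shared-look analysis brought the null ratio back to 0.98 to 1.01, with false wins near nominal. The cost is wording and coarser event times: at the planned 0.621 without masking, power was 73% against 74% with exact dates. Scans and patient care do not change.

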#### Primary endpoint analysis

For the primary endpoint analysis, observations will be censored at 30 months. The MPFS of the two arms will be compared using a Cox proportional hazards regression model to obtain a hazard ratio and accompanying 95% confidence interval. The stratification variables will be accounted for by including these as covariates in the Cox regression [21]. Furthermore, the proportional hazard assumption will be assessed.

For subgroup analysis, an interaction analysis will be conducted to test treatment effect modification with respect to several defined factors, such as number of metastases, type of metastases and location of lymph node metastases. These subgroup analyses should be considered for hypothesis generating rather than hypothesis testing since the trial is not designed to detect these heterogeneous treatment effects.

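### MPFS runs from randomisation but the scans are scheduled from radiotherapy, so an ADT lead-in that delays radiotherapy in arm 2 would pull the hazard ratio below 1 without any treatment effect

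*Protocol article*

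**What the plan says.** **Endpoint clock.** Under Primary endpoint, "MPFS is defined as the time from randomisation to the date of metastases progression", and the event takes the date of the PSMA PET/CT that shows it.

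**Assessment clock.** Under Imaging, scheduled scans are due "for patients without progression at 12 and 24 months after treatment". Table 2 is titled "Follow up after radiotherapy treatment" and its columns count months after RT, for PSA visits as well as scans. Scans are also triggered by PSA: "Follow-up PSMA PET/CT should be performed in case of biochemical progression", where the rise must be confirmed six weeks later.

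**Lead-in.** Under Androgen deprivation therapy (arm 2), "ADT should start no later than the first day of radiotherapy and no earlier than 12 weeks before the start of radiotherapy". Arm 1 has no counterpart. No interval from randomisation to radiotherapy, or from randomisation to the ADT injection, is given.

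**Analysis.** Under Primary endpoint analysis, "For the primary endpoint analysis, observations will be censored at 30 months". The arms are compared by Cox regression with the stratification variables as covariates.

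**The concern.** The endpoint and the scans that reveal it are counted from different dates, and the gap between those dates can depend on the randomised arm. A progression found at a scheduled scan is dated at that scan, not when it occurred. If arm-2 patients start radiotherapy later after randomisation than arm-1 patients, their two scheduled scans sit later on the MPFS clock. For some weeks arm-1 events are being recorded while arm 2 has not yet been scanned. The Cox model reads that as a lower hazard in arm 2. Adjustment for number of metastases, organ and local recurrence cannot remove a difference in scan calendar. What is at stake is the trial's only confirmatory comparison: a spurious ratio somewhat below 1, set against a planned ratio of 0.621.

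There is also an ambiguity. The Imaging section counts from treatment and Table 2 counts from RT. In arm 2, treatment includes six months of ADT. A site that counted from the end of ADT would place the second scan at least 6 + 24 = 30 months after the injection, at or beyond the censoring time. Table 2 favours the RT reading, but the Imaging text leaves the other open.

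**Working it through.** **1. The plan's own figure.** Inputs from Sample size: hazards 0.0330 and 0.0205 per month, hazard ratio 0.621, alpha 5%, power 80%, dropout 18% at 30 months.
- Events (Schoenfeld, two-sided): 4 × (1.960 + 0.842)² / (ln 0.621)² = 138.3, so 139.
- Dropout hazard: −ln(0.82)/30 = 0.00662 per month.
- Probability of an observed event by 30 months, λ/(λ+γ) × [1 − exp(−30(λ+γ))]: 0.579 and 0.421, mean 0.500.
- N = 139/0.500 = 278, against 280 stated. The figure reproduces, and the same settings are used below. The sidedness of alpha is not stated; two-sided reproduces N.

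**2. The mechanism by hand.** The permitted lead-in is 0 to 12 weeks, that is 0 to 84/30.44 = 2.76 months. Assume hazard 0.033 in both arms and radiotherapy ending 1 month after randomisation in arm 1, so that its first scheduled scan falls at month 13. Ignoring dropout, the share already progressed is 1 − exp(−0.033 × 13) = 34.9%, all dated near month 13. With a 6-week delay, arm 2 is scanned at month 14.38 and shows 1 − exp(−0.033 × 14.38) = 37.8%. With 12 weeks it is scanned at month 15.76 and shows 40.6%. So arm-1 events come first, which pulls the ratio down. The later scan also collects more events, which pushes it back up. This is why a longer delay is not always worse.

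**3. Simulation under no effect.** 140 per arm, hazard 0.033 in both, dropout as above, censoring at 30 months. Scans fall at 12 and 24 months after RT with a timing SD of 0.5 month. PSA-triggered scans follow the RT visits at 1, 3, 6, 12, 18 and 24 months by 1.5 months, in the stated share of patients. Unadjusted Cox model, 5000 trials per cell. The delay pattern, PSA-detectable share and timing SD are assumptions. Cells show hazard ratio / two-sided type I error.

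| Extra RT delay in arm 2 | Scheduled scans only | 30% PSA-detectable | 60% PSA-detectable |
|---|---|---|---|
| none | 1.00 / 5% | 1.00 / 5% | 1.00 / 5% |
| uniform 0–12 weeks | 0.89 / 11% | 0.94 / 7% | 0.98 / 5% |
| 6 weeks, all patients | 0.86 / 16% | 0.92 / 8% | 0.97 / 6% |
| 12 weeks, all patients | 0.89 / 11% | 0.96 / 6% | 1.00 / 5% |
| half 0, half 12 weeks | 0.94 / 7% | 0.98 / 5% | 1.00 / 6% |

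A repeat with a different seed agreed within 0.01 on the ratio and 2 percentage points on the error. With no PSA triggers, perfectly punctual scans give 0.84 to 0.89 (12% to 17%), and a timing SD of 1 month gives 0.90 to 0.94 (8% to 10%).

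**4. Lead-in running during the wait for radiotherapy.** Assume both arms wait 3 to 8 weeks for RT, and that a lead-in of 0 to 12 weeks delays RT only by its excess over that wait. The ratio is then about 0.94 (6% to 7%) with scheduled scans only, 0.97 (5% to 6%) with 30% PSA-detectable, and 0.98 to 0.99 (about 5%) with 60%. A lead-in of 0 to 6 weeks gives 0.99 to 1.00 and about 5% throughout.

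**5. The fix.** With scans and PSA visits both counted from randomisation, the ratio is 1.00 to 1.01 and the error 4% to 6%. With only the scans moved and PSA visits left on the RT clock, it is 0.99 to 1.03 and 5% to 6%.

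**The case against.** A reader might infer that arm 2 is scanned later by design and that the hazard ratio therefore favours ADT whatever happens. The document does not say that. The lead-in is permitted, not required, and ADT may start on the first day of radiotherapy. The 12 weeks bound the interval from ADT to RT, not from randomisation to RT. Radiotherapy needs a planning CT, sometimes MRI, and plan preparation in both arms, and ADT can run during that wait. All of this stands: the differential delay is possible, and its size is unknown.

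The larger figures also require that scheduled scans find nearly all progressions. The protocol calls for a scan at confirmed biochemical progression, and its Background reports biochemical recurrence in more than 60% of patients within two years of MDRT. At 60% PSA-detectable the bias nearly vanishes. This stands in part. The Background does not say that its recurrence definition matches the trial's trigger (PSA above the last pre-therapy value, confirmed), so 60% may not carry over. PSA visits are counted from RT as well, so triggered scans inherit any shift; the table already allows for this.

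It is tempting to add that ADT suppresses PSA and so delays triggered scans in arm 2. That is a separate mechanism, which would act even with no delay in radiotherapy, and it should not be counted here.

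Finally, interval-censored analyses are commonly left to the analysis plan, which is not at hand. Their absence from the article is not a fault. The mismatch of clocks is, because the article states both.

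**Conclusion.** The mismatch is real and stated in the text: MPFS counts from randomisation, scans and PSA visits count from RT, and only arm 2 has a permitted lead-in. Sites that follow these rules as written can date arm-2 progressions later for a reason unrelated to efficacy, and the planned covariates do not correct it.

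The size is conditional. With no treatment effect and the assumed delays, the hazard ratio lies between 0.86 and 0.94 (type I error 7% to 16%) if scheduled scans find all progressions, between 0.92 and 0.98 (5% to 8%) at 30% PSA-detectable, and between 0.97 and 1.00 (5% to 6%) at 60%. It is essentially 1 if the lead-in fits within the usual wait for radiotherapy. These ranges rest on assumed delay patterns, PSA-detectable shares and scan timing, none of which the article gives. The documents do not support a claim that the primary result is biased by design. The point is a recommended improvement, not a condition for the trial's validity.

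**What to change.** - Schedule the 12- and 24-month PSMA PET/CT from the date of randomisation in both arms, with one common window (for example ± 4 weeks). Toxicity and QoL visits can stay on the RT clock. PSA visits may move or stay; moving the scans alone removes nearly all of the difference. No treatment rule changes.
- In the Imaging section, state which date the scan intervals count from, so that it agrees with Table 2.
- For patients already scanned on the RT calendar, add a sensitivity analysis of MPFS by an interval-censored proportional hazards model, using actual scan dates from randomisation.
- Tabulate by arm the time from randomisation to start of RT and to each scan. This shows directly whether the delay occurred.

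The number of scheduled scans is unchanged. The cost is an amendment to Table 2 and the Imaging text and a notice to sites. Scan dates will no longer coincide exactly with RT-anchored visits. The 100 patients randomised by December 2021, and any since, may have followed the old calendar, so the final data would mix two schedules. The sensitivity analysis is there for that reason.
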